**2. During the past 4 weeks, how often have you had shortness of breath?**					

More than once a day ①	Once a day ②	3 to 6 times a week ③	Once or twice a week ④	Not at all ⑤	

**3. During the past 4 weeks, how often did your asthma symptoms (wheezing, coughing, shortness of breath, chest tightness or pain) wake you up at night or earlier than usual in the morning?**					

4 or more nights a week ①	2 or 3 nights a week ②	Once a week ③	Once or twice ④	Not at all ⑤	

**4. During the past 4 weeks, how often have you used your rescue inhaler or nebulizer medication (such as albuterol)?**					

3 or more times per day ①	1 or 2 times per day ②	2 or 3 times per week ③	Once a week or less ④	Not at all ⑤	

**5. How would you rate your asthma control during the past 4 weeks?**					

Not controlled at all ①	Poorly controlled ②	Somewhat controlled ③	Well controlled ④	Completely controlled ⑤	

#### Secondary outcomes

Measurement of lung function provides an assessment of the severity, reversibility, and variability of airflow limitation. Forced expiratory volume in 1 s (FEV1) and peak expiratory flow (PEV) will be used in this trial. Attack frequency also will be assessed. These outcomes also will be assessed before treatment and at days 90 in the treatment period. Follow-up visit will be at 3, 6 months after the last treatment session. Adverse event information will be collected at each clinic visit.

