**Methods/Design:**

This study is comprised of a multi-centre (12 centers in China), randomized, controlled trial with two parallel arms (A: heat-sensitive moxibustion; B: conventional drug). Group A selects heat- sensitive acupoints from the rectangle region which consist of two outer lateral lines of dorsal Bladder Meridian of Foot-Taiyang, and two horizontal lines of BL13(Fei Shu) and BL17 (Ge Shu);6 inch outer the first and second rib gap of anterior chest. Group B treats with fluticasone/salmeterol (seretide). The outcome measures will be assessed over a 3-month period before each clinic visit at days 15, 30, 60, and 90. Follow-up visit will be at 3, 6 months after the last treatment session. Adverse event information will be collected at each clinic visit.

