### Statistical methods

#### Statistical analysis plan

We will conduct analysis on an intention-to-treat basis, including all randomized participants with at least one measurable outcome report. Analyses will be conducted using 2-sided significance tests at the 5% significance level. An analysis using the Cochran-Mantel-Haenszel procedure will be done to asses center effect. The statistician conducting the analyses will remain blind to treatment group and data will only be unblinded once all data summaries and analyses are completed. All analyses will be conducted in the SAS statistical package program (ver. 9.1.3).

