#### Outcome data

For primary and secondary outcome measures, these will be summarized descriptively (mean, SD, median, minimum and maximum) at each time point by treatment group. The t-test, Mann-Whitney U and Wilcoxon test were used for comparison of variables, as appropriate.

All adverse events reported during the study will be included in the case report forms; the incidence of adverse events will be calculated. The percentage of subjects with adverse events in each group will be calculated and compared using the chi-squared test or Fisher's exact test.

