##### Dropped or missing data

Reasons for dropped or missing data will be explored by descriptively. Missing data will be replaced according to the principle of the last observation carried forward.

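### For patients lost before day 90, last observation carried forward turns the pre-treatment attack frequency into the day-90 result, which dilutes the comparison if dropout is equal and can bias it either way if it is not

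*Protocol article*

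**What the plan says.** The Secondary outcomes section names FEV1, peak expiratory flow and attack frequency: "Attack frequency also will be assessed". For all three it states "These outcomes also will be assessed before treatment and at days 90 in the treatment period", and then "Follow-up visit will be at 3, 6 months after the last treatment session". The Primary outcome section gives ACT further assessments at days 15, 30 and 60; the Secondary outcomes section does not.

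The Outcome data section covers both kinds of outcome ("For primary and secondary outcome measures, these will be summarized descriptively") and names the tests: "The t-test, Mann-Whitney U and Wilcoxon test were used for comparison of variables, as appropriate". The Dropped or missing data section has one rule for everything: "Missing data will be replaced according to the principle of the last observation carried forward". The analysis set is broad, "including all randomized participants with at least one measurable outcome report". The Follow-up data section, which compares the groups at 3, 6 and 9 months, expects 20% loss, split neither by arm nor by time.

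The abstract differs on timing: "The outcome measures will be assessed over a 3-month period before each clinic visit at days 15, 30, 60, and 90".

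**The concern.** Each sentence is ordinary alone; the fault comes from combining them. A patient who attends at day 15, completes an ACT and then leaves has an outcome report and so belongs in the analysis set. On the Secondary outcomes schedule, that patient's only attack value predates randomisation. The carry-forward rule makes it the day-90 result. Attacks on treatment before leaving are not used, and neither is the length of time observed.

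The same rule governs FEV1 and peak flow. With attacks it also throws away information: events before leaving can be counted, and the time over which they were counted is known.

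The stake is how a small or non-significant difference is read. The Sample size section is built on non-inferiority, and the Discussion describes the aim as a treatment as good as the conventional drug. In that setting, a rule that shrinks a true difference helps the conclusion sought. A rule that can also create a difference makes the result hard to read in either direction.

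**Working it through.** **The plan's own figure.** The article gives no expected attack rate, effect or margin for attack frequency. Its margin of 0.15 concerns ACT. There is nothing to reproduce, so the check is on the expected effect of the rule.

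**Inputs from the article.** Assessment before treatment and at day 90; last observation carried forward without exception; 20% anticipated loss; 144 per group.

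**Assumptions (the article gives no values).** Arm A is moxibustion and arm B the drug. Baseline mean b = 6 attacks in both arms. On-treatment means are μA = 3 and μB = 2, a true difference of 1.0. Leavers before day 90 are a random share, dA and dB.

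**Formula.** The expected day-90 mean in an arm is (1 − d) × μ + d × b. Hence

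- equal dropout: difference = (1 − d) × (μA − μB), since the baseline terms cancel;
- no true effect (μA = μB = μ): difference = (dA − dB) × (b − μ), which is zero only if dropout is equal or there is no change from baseline.

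**Results.**

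| Dropout A / B | Arm A | Arm B | Difference (true 1.0) |
|---|---|---|---|
| 10% / 10% | 0.9×3 + 0.1×6 = 3.3 | 0.9×2 + 0.1×6 = 2.4 | 0.90 |
| 20% / 20% | 0.8×3 + 0.2×6 = 3.6 | 0.8×2 + 0.2×6 = 2.8 | 0.80 |
| 10% / 30% | 0.9×3 + 0.1×6 = 3.3 | 0.7×2 + 0.3×6 = 3.2 | 0.10 |
| 30% / 10% | 0.7×3 + 0.3×6 = 3.9 | 0.9×2 + 0.1×6 = 2.4 | 1.50 |

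With no true effect (3 against 3), 10%/30% dropout gives (0.1 − 0.3) × (6 − 3) = −0.60, and 30%/10% gives +0.60.

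**On the ratio scale.** Assume baseline 6, drug 3.0 and moxibustion 4.05, a true ratio of 1.35.

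- 20%/20%: (0.8×4.05 + 0.2×6)/(0.8×3 + 0.2×6) = 4.44/3.60 = 1.23.
- 30% moxibustion / 10% drug: (0.7×4.05 + 0.3×6)/(0.9×3 + 0.1×6) = 4.635/3.30 = 1.40.

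**Simulation.** Overdispersed counts (dispersion 0.8, assumed), 144 per arm, 1500 runs, means 6 at baseline and 3 against 2 on treatment. With 20% dropout in both arms, t-test power is 0.86 on full data, 0.78 on completers and 0.42 after carry-forward (Mann-Whitney after carry-forward 0.57). With 10%/30% dropout, t-test power after carry-forward is 0.06. With no true effect, the t-test after carry-forward rejects in 4.3% of runs at 20%/20% dropout and in 24% at 10%/30%.

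**The case against.** Several points on the other side stand.

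- **Direction.** A reader might infer that the rule always pulls the arms together and so hides a disadvantage of moxibustion among those who leave because of it. The article does not support that: it gives no dropout by arm. If more patients left the moxibustion arm, the second ratio above (1.40 against a true 1.35) shows the disadvantage exaggerated.
- **Tests.** A reader might infer that t or rank tests are wrong for attacks. Over equal, complete windows they are valid, and the article says they are used as appropriate. The 4.3% rejection at equal dropout agrees. Nor does the article plan to compare raw partial counts, so errors of that method are no charge against it.
- **Definition.** The article gives no unit or window for attack frequency, and a condensed article may leave this to the full protocol. If it is a fixed recall window, unequal observation time matters less. The substitution of a pre-treatment value remains.
- **Schedule.** On the abstract's schedule an on-treatment value could be carried forward for many leavers. That would weaken the point, though an earlier window would still stand in for day 90. The two sections conflict, and neither says which governs.
- **Size of loss.** Patients lost after day 90 carry their day-90 value. If the 20% covers nine months, loss before day 90 is smaller.

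The objection that a separate analysis plan may settle this carries little weight. The carry-forward rule and the tests are stated here, in the article's Statistical methods section, without exception.

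**Conclusion.** The point holds as a fault of carry-forward from baseline, not of the named tests. On the Secondary outcomes schedule, anyone lost before day 90 is analysed with a pre-treatment attack frequency, and attacks on treatment are ignored. With similar baselines and equal dropout d before day 90, the difference shrinks to (1 − d) of its true size: 0.90 at 10% and 0.80 at 20%, the latter an upper case. With unequal dropout the bias can go either way and can arise with no true effect. The (1 − d) result needs no attack rates. The other figures rest on assumed means and dispersion, and all of them assume leavers are a random share of their arm. This is a secondary outcome, so the point is a worthwhile improvement rather than a threat to the primary analysis.

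**What to change.** 1. Reconcile the abstract's assessment schedule with the Secondary outcomes section.
2. Exempt attack frequency from last observation carried forward.
3. At the visits already held (days 15, 30, 60 and 90, and follow-up), record attacks since the last visit and days observed. The article describes only a baseline diary, so a short question at the visit is the realistic source.
4. Analyse by negative binomial regression on treatment, centre and baseline attacks, with log observed days as offset. Report the rate ratio with 95% CI, and the number and timing of losses by arm.
5. Add a simple sensitivity analysis. The model assumes that, given the covariates, leaving is unrelated to the later attack rate. One option is to multiply leavers' unobserved rate by a stated range of factors, separately by arm.

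The cost is one question at existing visits and one model specification in the SAS package already planned.

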### Design

A multi-centre, randomized, two parallel arms (group A and B) and assessor blinded, positive controlled trial will be conducted at the twelve centers in China (Table 2).

**Table 2 T2:** List of 12 clinical centers

Name	City	Province
Affiliated Hospital of Jiangxi University of Traditional Chinese Medicine(TCM)	Nanchang	Jiangxi

Guangdong Hospital of Traditional Chinese and Western Medicine	Foshan	Guangdong

Wuhan the First Hospital	Wuhan	Hubei

Guangdong Hospital of TCM	Guangzhou	Guangdong

Guangzhou University of TCM	Guangzhou	Guangdong

Guangdong Disabled Soldier Hospital	Guangzhou	Guangdong

Affiliated Hospital of Shandong University of TCM	Jinan	Shandong

Suzhou Hospital of TCM	Suzhou	Jiangsu

The First Affiliated Hospital of Zhejiang University of TCM	Hangzhou	Zhejiang

The First Affiliated Hospital of Chongqing Medical University	Chongqing	Chongqing

The First Affiliated Hospital of Nanchang University	Nanchang	Jiangxi

Nanchang Hospital of Traditional Chinese and Western Medicine	Nanchang	Jiangxi

The study will be sequentially conducted as follows: a run-in period of one week prior to randomization, a treatment period of 90 days, and a follow-up period of six months. At the end of the run-in period, participants will be randomized to the heat-sensitive moxibustion group or the drug group by the central randomization system (Figure 1). This system is provided by China Academy of Chinese Medical Sciences, which adopted the computer telephone integration (CTI) technology to integrate computer, internet and telecom. The random number list will be assigned by interactive voice response (IVR) and interactive web response (IWR) [31]. The success of blinding will be assessed at each participant's last visit. Assessor who did not participate in the treatment and who is blinded to the allocation results will perform the outcome assessment.

**Figure 1 F1:**
[figure not shown]
**The flow diagram is intended to depict the passage of participants through this RCT**.

### Eligibility

#### Inclusion criteria

According to the guideline of asthma treatment and prevention in China (GATPC) [32], patients are divided into three types, including acute exacerbation, chronic persistent and clinical remission. Severity grade of asthma in GATPC is described in Table 3. Our trial will only choose participants with chronic moderate persistent asthma (Figure 1).

**Table 3 T3:** Clinical classification of severity in GATPC

Characteristic	Intermittent (Grade I)	Mild (Grade II)	Moderate (Grade III)	Severe (Grade IV)
**symptoms**	Less than once week	More than once week, < once a day	Everyday	Everyday

**Limitation of activities and sleep**	Transient	May be affect activities and sleep	Affect activities and sleep	Frequent

**Nocturnal of symptoms/awakening**	Less than twice a month	More than twice a month, < once a week	More than once week	Frequent

**Lung function(PEF or FEV1)**	≥80% predicted (FEV1)or personal best (PEF); mutation rate < 20%	≥80% predicted (FEV1)or personal best (PEF); mutation rate 20%~30%	60%~79% predicted (FEV1)or personal best (PEF); mutation rate > 30%	< 60% predicted (FEV1)or personal best (PEF); mutation rate > 30%

Patients will be required to complete the baseline asthma diary. Written informed consent will be obtained from each participant. Participants 18~65 years of age will be recruited from outpatient and inpatient in 12 centers. Standard of diagnosis listed as follows: (1) Common signs and symptoms of asthma include: recurrent wheezing, coughing, trouble breathing, chest tightness; (2) Symptoms that occur or worsen at night, and symptoms that are triggered by cold air, exercise or exposure to allergens; (3) Scattered or diffuse expiratory wheezing sound could be heard in the lungs in attack; (4) The above symptoms will be relieved or disappear after treatment; (5) Ruling out conditions other than asthma; (6) When typical clinical symptoms can not be observed, lung function tests should be used to confirm, such as positive challenge test, positive bronchodilator test(an increase in FEV1 of ≥12% and ≥200 ml), and mutation rate of PEF≥20% one day/two weeks. Since the research involves moderate asthma (grade III), the inclusion criteria will restrict the following conditions: According to the below GATPC diagnosis standard, meanwhile, heat-sensitivity appears within the rectangle area which consist of two outer lateral lines of dorsal Bladder Meridian of Foot-Taiyang, and two horizontal lines of BL13 (Fei Shu) and BL17 (Ge Shu); 6 inch outer the first and second rib gap of anterior chest. Participants will be instructed to stop asthma symptomatic relief medication during the run-in and treatment periods and will be provided the usual care instruction for asthma.

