## Background

Asthma is a common chronic inflammatory disease of the airways characterized by variable and recurring symptoms, airflow obstruction, and bronchospasm [1]. It is also a complex disease involving many cells and mediators[2]. Asthma affects 300 million people worldwide[3], with an increasing prevalence in Western Europe(5%) and the USA(7%) in particular[4,5]. Despite the fact that there is still no cure for asthma, it has been established in a great number of small and large studies that many patients can reach a good asthma control with controller treatment [6]. Generally speaking, Medications used to treat asthma are divided into two general classes: quick-relief medications used to treat acute symptoms and long-term control medications used to prevent further exacerbation [7]. The therapeutic options available for patients with asthma depend on the severity of the condition. Although the symptoms can be controlled by drug treatment in most patients, effective low-risk, non-drug strategies could constitute a significant advance in asthma management [1-3]. Therefore, an increasing number of patients with asthma are attracted by complementary and alternative medicine (CAM) [8]. A survey showed that roughly 50% of asthma patients used some form of unconventional therapy [9].

Acupuncture has traditionally been used in asthma treatment in China and is increasingly applied for this purpose in Western countries. Moxibustion is a traditional Chinese method of acupuncture treatment, which utilizes the heat generated by burning Moxa (it is also called Mugwort or Moxa) to stimulate the acupuncture points. The technique consists of lighting a moxa-stick and bringing it close to the skin until it produces hyperemia due to local vasodilatation. The intensity of moxibustion is just below the individual tolerability threshold. Moxibustion has anti-inflammatory or immunomodulatory effects against chronic inflammatory conditions in humans [10]. Moxibustion method for treatment of asthma diverse curative effect and its mechanism may be due to improve lung function, antagonize of inflammatory mediators, modulate of immune function, regulate the role of cyclic nucleotide levels, and can also affect the neuroendocrine network and inflammatory cells[11-14]. Therefore, these inflammatory substances may be reduced and weakened by moxibustion. Especially for chronic persistent asthma, moxibustion may get a better effect.

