### Outcome measures

#### Primary outcome

At present, the goal of asthma care is to achieve and maintain control of clinical manifestation of the disease [27,28]. Hence, we use Asthma Control Test (ACT) to quickly access asthma control, a simple 5-question tool that is completed by the patient and parents/caregivers and recognized by the National Institutes of Health (Table 1)[29,30]. Patients should write the number of each answer in the score box provided, and then add up each score box for your total. ACT will be assessed before treatment and at days 15, 30, 60, and 90 in the treatment period. Follow-up visit will be at 3, 6 months after the last treatment session.

**Table 1 T1:** Asthma Control Test (ACT) for people 12 yrs and older.

1. In the past 4 weeks, how much of the time did your asthma keep you from getting as much done at work, school or at home?					Score
All of the time ①	Most of the time ②	Some of the time ③	A little of the time ④	None of the time ⑤	

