#### Drug group

In recent years, considerable insight has been gained in to the optimal management of adult asthma. Those with persistent asthma are usually not well controlled without inhaled corticosteroids (ICS). Adding a long-acting beta-agonist (LABA) to ICS appears to be well controlled [33]. The combination of an ICS and LABA is preferred in these patients, and is better than doubling or even quadrupling the dose of ICS to achieve better asthma control and reduce exacerbation risks [34,35]. Two such combinations, salmeterol xinafoate and fluticasone propionate (SFC, Seretide(tm)) and formoterol and budesonide (FBC, Symbicort(tm)) are widely used and have been shown to be effective in controlling asthma of varying severity in adults and children[36-38].

Therefore, we selected the Seretide Accuhaler, containing two medicines, fluticasone propionate and salmeterol xinafoate, which is the mainstay of current asthma treatment. This drug is recommended by GINA as a regular treatment. Our trial uses salmeterol/ﬂuticasone 50 μg/250 μg twice a day. Patients receive the treatment for a total of 180 sessions over 90 days.

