#### Sample size

We wished to estimate the sample size according to non-inferiority clinical trial between the heat-sensitive and drug group. Sample size depends on the level of confidence chosen, the risk of type II error (or desired power), and δ. The parameter margin of non-inferiority δ can be specified as a difference in means or proportions. It is often chosen as the smallest value that would be a clinically important effect. To determine δ, we carried out a small sample pilot study previously. The primary endpoint chosen was ACT. The result of outcome showed difference in means between the two groups approximately was 0.45. The choice of δ = 0.15 (30% of Δ) appeared to be reasonable based on clinical relevance and statistical judgment.

If we apply a two-sided 5% significance level(δ = 0.15, α = 0.05, β = 0.2), 95% power the calculated required sample size is approximately 120 participants in each group, according to the following equation. Allowing for a 20% loss to follow up, a total of 144 participants will be required in each group, with 288 participants in total.

$$n=2\times \frac{{\left(U_{\alpha }+U_{\beta }\right)}^{2}}{\gamma^{2}}\times P(1-P)$$

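### Patients with daily asthma symptoms are told to stop relief medication for 97 days with no stated exception for an attack, and the rule fixes ACT item 4 at day 90 for those who comply

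*Protocol article*

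**What the plan says.** The Inclusion criteria section states that participants are "instructed to stop asthma symptomatic relief medication during the run-in and treatment periods". The sentence is not limited to one arm, to routine use, or to a washout before visits. It goes on to say that they will also receive usual care advice for asthma, which is not described. The Design section sets the two periods: "a run-in period of one week prior to randomization, a treatment period of 90 days".

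Other parts of the article bear on this rule:

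- **Background** describes one of the two classes of asthma drug as "quick-relief medications used to treat acute symptoms", and sets it apart from long-term control drugs.
- **Inclusion criteria** says: "Our trial will only choose participants with chronic moderate persistent asthma". Table 3 gives this grade daily symptoms, night symptoms more than once a week, and FEV1 or PEF at 60 to 79%.
- **Treatment protocol** lists moxibustion alone for group A. For group B it gives salmeterol/fluticasone twice a day. The Drug group section also says: "Those with persistent asthma are usually not well controlled without inhaled corticosteroids (ICS".
- **Table 1, ACT item 4** asks: "During the past 4 weeks, how often have you used your rescue inhaler or nebulizer medication (such as albuterol". The answers run from 1 (three or more times per day) to 5 (no use).
- **Primary outcome** gives the schedule: "ACT will be assessed before treatment and at days 15, 30, 60, and 90 in the treatment period". The Follow-up data section places the primary comparison at 3 months.
- **Secondary outcomes** includes attack frequency.

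**The concern.** There are two problems, and the first stands without the second.

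**Safety.** The article itself describes quick-relief drugs as the treatment for acute symptoms, and then tells patients who have symptoms every day to stop symptomatic relief for the whole of run-in and treatment. Attacks are expected, since their frequency is an outcome. A patient who has one must either go without quick relief or depart from the protocol. The exposure is greatest in the moxibustion arm, which is assigned no controller although the article says that persistent asthma is usually poorly controlled without inhaled corticosteroids. The drug arm receives a regular twice-daily combination but no stated quick relief either.

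**Measurement.** The primary outcome counts rescue use as a sign of poor control. If rescue use is forbidden throughout the recall window, item 4 records obedience to the instruction instead of asthma control. With full compliance it takes the same value in both arms. The Sample size section says that the aim was to "estimate the sample size according to non-inferiority clinical trial between the heat-sensitive and drug group". In a non-inferiority trial, an item that cannot differ between arms tends, on that item, to make the treatments look alike.

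**Working it through.** The plan gives no figure of its own on this point, so there is none to reproduce. The check uses day counts and the ACT scoring.

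**Inputs.** Run-in 7 days and treatment 90 days (Design). Recall period 4 weeks, each item scored 1 to 5 (Table 1). Assessments before treatment, at days 15, 30, 60 and 90, and at 3 and 6 months after treatment (Primary outcome). 144 patients per group, 288 in total (Sample size).

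**1. Length of the ban.** 7 + 90 = 97 days.

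**2. Overlap of the recall window with the ban.** The window is 4 × 7 = 28 days. The ban covers the 7 run-in days and treatment days 1 to 90.

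| Assessment | Days of the window inside the ban |
|---|---|
| Before treatment | 7 of 28 (run-in only) |
| Day 15 | 15 + 7 = 22 of 28 |
| Day 30 | days 3 to 30: 28 of 28 |
| Day 60 | days 33 to 60: 28 of 28 |
| Day 90 (primary) | days 63 to 90: 28 of 28 |
| 3 and 6 months after treatment | 0 of 28 |

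Item 4 is therefore fully determined for a compliant patient at days 30, 60 and 90, and only partly constrained at baseline and day 15.

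**3. Effect on the score range.** Five items scored 1 to 5 give a total from 5 to 25, a span of 20 points. Item 4 contributes 5 − 1 = 4 of these, and 4/20 = 20%. With item 4 held at 5, the lowest possible total is 4 × 1 + 5 = 9, so the range becomes 9 to 25, a span of 16.

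**4. Effect on the comparison.** Without the ban, item 4 can differ between arms by at most 4 points. With full compliance in both arms it differs by 0. Since only 7 of the 28 baseline days are under the ban, a change from baseline can also contain a gain on item 4 produced by the instruction.

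**5. What cannot be computed.** The article gives no rate of compliance, rescue use or attacks, so no shift in arm means is estimated. The 4 points are the most the item could contribute and are not an expected effect.

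**The case against.** The strongest reply is that the article condenses a fuller protocol. Rescue and exacerbation handling is commonly left to that document, and the usual care advice in the same sentence is a natural place for it. The English is also loose: the sentence may mean only that patients give up their pre-trial symptomatic drugs at run-in. Keeping an ACT item on rescue use and counting attacks would fit a trial that expected some rescue use.

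This leaves the intent of the rule open but does not cure the wording. The article is not merely silent on rescue. It states a stop, in both arms, for drugs that its Background associates with acute symptoms. The care advice is an additional provision that is not described, and nothing says that it lifts the stop. If a fuller protocol does hold a rescue rule, the published sentence conflicts with it and still needs correcting.

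Three limits stand:

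- The article does not say that existing inhaled maintenance treatment is withdrawn. The moxibustion arm is assigned no controller by the trial, but it is not shown that every patient in it is without one.
- Item 4 is fixed only for patients who comply, and patients with daily symptoms may well not. With partial compliance the item mixes adherence with control.
- The other four ACT items can still move. Without rescue, symptoms may separate the arms more on those items, so neither the direction nor the size of the net effect on the total score is established.

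**Conclusion.** The concern holds. As written, the rule keeps relief medication from all 288 planned patients for 97 days with no stated exception for acute symptoms or an attack, and 144 of them are assigned no controller for the 90 treatment days. Followed literally, this is a patient-safety fault, and it must be fixed whatever one thinks of the measurement point.

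The measurement point is conditional on compliance. For compliant patients, ACT item 4 is 5 at days 30, 60 and 90, including the primary time point. This removes 4 of the 20 points of the range from any possible contrast. No net bias in the total score is claimed.

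The conclusion rests on reading symptomatic relief medication as the quick-relief class named in the Background, which is the plain reading.

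**What to change.** Amend the sentence in the Inclusion criteria section so that relief medication is permitted at any time, in both arms, for acute symptoms or an attack, and only routine use is restricted during run-in and treatment. Change the patient instruction to match.

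At days 15, 30, 60 and 90, record any relief medication and systemic treatment used, and report it by arm. ACT item 4 already gives a frequency band for rescue use, but it does not record which drug was taken or any systemic treatment. State that patients who use relief medication stay in follow-up through the day-90 ACT.

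The cost is one amended sentence, one patient instruction and one added question at four visits that already exist; no new diary is needed. The change has to be passed to 12 centres and the ethics boards concerned. Some relief use will then occur and will lower item 4 for those patients, which is what the item is meant to register.
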